## Abstract

**Background:**

The prevalence rate of hypertension in the Chinese population is on the rise, and the control rate of hypertension is low. International guidelines, including the 2018 Chinese Guidelines for the Management of Hypertension, recommend optimized drug selection and combination therapy for patients with stage 2 hypertension and blood pressure ≥ 160/100 mmHg, including valsartan/amlodipine (Val/Aml). The traditional Chinese medicine (TCM) compound Tengfu Jiangya tablet (TJT; No. Z20110021, Shandong Provincial Food and Drug Administration) is prepared in the medical institution of Affiliated Hospital of Shandong University of Traditional Chinese Medicine. It is an effective compound preparation of TCM for the treatment of hypertension in the national clinical research base of TCM. The aim of this study was to evaluate the efficacy and safety of TJT combined with Val/Aml in the treatment of stage 2 hypertension with hyperactivity of liver yang.

**Methods:**

This randomized double-blind, placebo-controlled, multicenter trial will be conducted with a total of 288 participants with stage 2 hypertension at seven clinical trial centers. The stratified random method will be used, and the subcenter will be taken as the stratification factor. Eligible patients will be randomly assigned (1:1) into groups receiving either TJT or placebo three times daily for 28 days, both combined with Val/Aml 80/5 mg. The primary efficacy endpoint is the reduction in the mean sitting systolic blood pressure (msSBP) and the mean sitting diastolic blood pressure (msDBP) from baseline to week 4. Adverse events and laboratory test results will be monitored throughout the trial.

**Discussion:**

This is the first placebo-controlled randomized trial conducted to evaluate the efficacy and safety of a Chinese herbal extract combined with Val/Aml in patients with stage 2 hypertension. Our study may help to provide evidence-based recommendations of a complementary preventive measure for stage 2 hypertension.

**Trial registration:**

Chinese Clinical Trial Registry ChiCTR2000030611. Registered on 8 March 2020

**Supplementary Information:**

The online version contains supplementary material available at 10.1186/s13063-022-06089-z.

## Administrative information

*Trials* guidance: please include this text in your protocol just above the administrative information table:

Note: the numbers in curly brackets in this protocol refer to SPIRIT checklist item numbers. The order of the items has been modified to group similar items (see http://www.equator-network.org/reporting-guidelines/spirit-2013-statement-defining-standard-protocol-items-for-clinical-trials/).

## Introduction

### Background and rationale {6a}

Hypertension is a common, chronic, noncommunicable disease caused by the interaction of many factors; it is also the most important and controllable risk factor for cardiovascular disease. Hypertension causes a heavy burden of disease [1]. According to global data, from 1975 to 2015, the number of people suffering from hypertension in the world increased from 594 million to 1.1 billion. There are 226 million people with hypertension living in China; the proportion of stage 2 hypertension is as high as 11.0% [2]. A prospective cohort study (China Kadoorie Biobank Study) showed that the diagnosis rate, treatment rate, and control rate of hypertension in Chinese adults are significantly lower than those in the Western population, and the rate of noncompliance and mortality are higher [3]. At present, improving the attainment rate of blood pressure (BP) in hypertensive patients is the most important task in the health management of cardiovascular disease; BP control of patients with stage 2 hypertension is still challenging [4]. As shown by VALUE, FEVER, and other studies, effective BP reduction within 4 weeks provides clear cardiovascular benefits, significantly reducing all-cause death, while reaching the target at 3 and 6 months does not reduce all-cause death [5, 6]. Therefore, international guidelines recommend that patients with stage 2 hypertension should start combined antihypertensive therapy and implement the antihypertensive treatment strategy based on single-compound preparation (SPC) to reduce the burden of tablets and improve compliance to further strengthen the control of BP; they also recommend a positive evaluation (a hypotension evaluation period of 2–4 weeks) to achieve the standard BP early, ideally within 4 weeks [7, 8].

Clinical and basic research has demonstrated that changes in vascular function and structure occur early in hypertensive diseases, including vascular endothelial cell damage, vascular endothelial dysfunction, abnormal vasoconstriction, and vascular remodeling [9, 10]. In addition to the development of hypertension, progressive damage and deterioration in vascular endothelial function and structure further facilitate the development of hypertension and increase the risk of cardiovascular events, including myocardial infarction, heart failure, and stroke. Thus, protecting vascular endothelial cells and correcting endothelial dysfunction have emerged as promising therapeutic targets for achieving standard BP early and treating hypertension [11].

Traditional Chinese medicine (TCM) is an important part of complementary and alternative medicine. Studies have shown that Chinese herbal medicine can play a role in protecting vascular endothelial cells and correcting endothelial dysfunction through multiple pathways and targets [12]. TCMs in the treatment of hypertension can be combined with antihypertensive drugs. This plays a positive role in reducing the dosage of antihypertensive drugs, enhancing the curative effect and BP stability [13]. In addition, in different periods of the occurrence and development of hypertension and different syndrome types, approximately 87.23% of patients had liver-yang hyperactivity syndrome [14].

Tengfu Jiangya tablets (TJTs) are successfully prepared by modern preparation technology to extract the effective antihypertensive components of *Uncaria rhynchophylla* and *Semen Raphani*. The main indication of TJT is hyperactivity syndrome of liver yang in hypertension. In a previous study [15–18], based on the metabonomics and proteomics techniques, we found that TJT may reduce BP by improving the production of NO and might exhibit additional cardiovascular protective effects by improving vascular endothelial inflammation and vascular remodeling. The molecular mechanism is mainly related to the kallikrein-kinin pathway, lipid metabolism pathway, and PPARγ signal transduction pathway. In an ongoing multicenter, randomized, double-blind clinical trial (ChiCTR-IIR-17011940) of TJT for the treatment of liver-yang hyperactivity in stage 1 hypertension, a preliminary analysis of the results showed that the antihypertensive effect of TJT was better than that of placebo. In addition, other small-sample randomized controlled trials also showed that TJT improved the clinical symptoms of hypertensive patients with hyperactivity of the liver and lower BP [19]. However, there is still a lack of high-quality evidence in large-sample, blinded, randomized, placebo-controlled clinical trials for stage 2 hypertension to reasonably evaluate whether TJT as an adjuvant treatment of ARB/CCB and SPC can further promote the early achievement of BP and improve clinical symptoms and patient compliance in patients with stage 2 hypertension.

Therefore, this study will involve a multicenter, double-blind, randomized, placebo-controlled method to evaluate the efficacy and safety of TJT-assisted Val/Aml in the treatment of stage 2 hypertension, providing a practical basis for the prevention and treatment of hypertension.

A completed SPIRIT checklist is available as a supplement (Additional file 1).

### Objectives {7}

The aims of our study were to evaluate the clinical efficacy and safety of TJT combined with Val/Aml SPC in the treatment of essential hypertension (stage 2) with hyperactivity of liver yang and to observe whether Val/Aml combined with TJT can further promote the early achievement of BP and improve clinical symptoms and patient compliance in patients with stage 2 hypertension compared with Val/Aml combined with placebo.

### Trial design {8}

This multicenter, double-blind, randomized, placebo-controlled, superiority trial was reviewed and approved by the Ethics Committee of the Affiliated Hospital of Shandong University of Traditional Chinese Medicine [approval registration number (2019) 伦审 (064) 号-KY] and registered in the Chinese Clinical Trial Registry (ChiCTR2000030611, version 2.0, dated 8 August 2020). The Chinese Clinical Trial Registry is a primary registry of the WHO ICTRP network and includes all items from the WHO Trial Registration dataset that are available at the link (http://www.chictr.org.cn/listbycreater.aspx). The trial will be conducted according to the principles of the Declaration of Helsinki and Good Clinical Practice Guidelines. In addition, we will comply with the Consolidated Standards of Reporting Trials (CONSORT) Extension of Chinese Herbal Medicine Formulas 2017 [20] when reporting the results. This study planned to recruit 288 subjects who will be randomly assigned in a 1:1 ratio.

An overview of the study procedures is shown in Fig. 1.

**Fig. 1 Fig1:**
[figure not shown]
Flowchart of this study

## Methods: participants, interventions, and outcomes

### Study setting {9}

The trial will be conducted in seven centers in Shandong Province, China, and all these hospitals and their ethics approvals are shown in Additional file 2. A total of 288 participants will be recruited. All the patients will provide written informed consent before participating in this study; recruited patients will be randomly divided into a treatment group (treated with Val/Aml and TJT) or a control group (treated with Val/Aml and placebo) in a 1:1 ratio. After the consent of participants is obtained, a trial will be conducted, including a run-in period of 2 weeks and a treatment period of 4 weeks. The onsite follow-up test of the research center will be conducted at 2 and 4 weeks after random grouping. In addition, telephone follow-up will be conducted on day 3 and week 3.

### Eligibility criteria {10}

#### Diagnostic criteria

The diagnostic criteria for primary stage 2 hypertension are based on the 2018 Chinese Guidelines for the Management of Hypertension (2018 revised edition) [21]. The diagnostic criteria for hyperactivity of liver yang in hypertension are based on the Hypertension TCM syndrome Diagnosis Scale developed by the National Hypertension TCM Clinical Research Base [22]. (Additional file 3)

#### Inclusion criteria

The following are the inclusion criteria:
Age ≥ 18 years and ≤ 65 years, male or femaleAt the same time, conforming to the diagnostic criteria for stage 2 hypertension [21] and the TCM syndrome differentiation criteria for liver-yang hyperactivity syndrome [22]For patients with primary stage 2 hypertension diagnosed according to established guidelines [21], BP that satisfies any one of the following three criteria:
Patients who have SBP 160–179 mmHg and/or diastolic BP (DBP) 100–109 mmHg, without prior use of any antihypertensive drugsPatients who have been clearly diagnosed with essential hypertension and whose BP is not up to standard after 3 months of improved lifestyle or other forms of nondrug therapy are maintained at 160–179/100–109 mmHgPatients who have been clearly diagnosed with essential hypertension and whose BP is still not up to the standard BP after 3 months of improved lifestyle or other forms of nondrug therapy and oral antihypertensive drugs maintain at 160–179/100–109 mmHgPatients must have had a definite diagnosis of hypertension for more than 3 monthsPatients will be informed about the trial and should voluntarily sign a consent form.

#### Exclusion criteria

The following are the exclusion criteria:
Secondary hypertensionParticipation in other clinical trials in the previous 3 months.The following diseases or organ damage within 6 months prior to screening: cardiovascular disease (unstable angina pectoris, heart failure, valvular disease, myocardial infarction), cerebrovascular disease (stroke, transient ischemic attack), hypertensive encephalopathy, retinopathy (with or without apparent papillary edema), aortic aneurysm, or aortic dissecting aneurysm artery occlusive disease symptomsPregnancy, preparing for pregnancy, and lactatingAllergies to multiple drugs or having an allergic constitutionMental illness, alcoholism, and/or psychoactive substance abuse and dependenceSevere liver disease or aspartate aminotransferase (AST) or alanine aminotransferase (ALT) ≥ normal upper limit. Severe kidney disease or creatinine level ≥ 2.0 mg/dL. Uncontrolled diabetes with HbA1c ≥ 9% or fasting glucose ≥ 160 mg/dLHaving received Val/Aml (80/5 mg) and other ARB/CCB type combination drugs and still having level 2 or above BP

#### Suspension criteria

The following are the suspension criteria:
Poor compliance of patients.The mean sitting SBP (msSBP) ≥ 200 mmHg and/or the mean sitting DBP (msDBP) ≥ 120 mmHg will result in exclusion at any time during the study period.Adverse events (AEs), complications, or physiological changes that are fatal.Use of prohibited drugs or treatments that may affect the analysis of results during the trial.Voluntary withdrawal.Incomplete data.Withdrawal due to various reasons, such as failure to participate in the follow-up.

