#### Criteria for discontinuing or modifying allocated interventions {11b}

Discontinuation criteria are withdrawal of consent, subsequent occurrence of a suspension criteria criterion (e.g., use of prohibited drugs), lack of compliance, and medical problems for stopping the intervention.

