#### Procedure for unblinding if needed {17b}

The researcher can open the blinding code only when the subject has serious adverse events or other special or emergency events, which necessitates knowing the specific grouping of the subjects before treatment. Researchers should contact the ethics committee to report the reasons for unblinding and record the date of unblinding, treatment, and final results in the CRF form. The subjects should discontinue the study after unblinding. The main investigator will decide whether the research protocol needs to be revised according to safety data after unblinding.

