## Statistical methods

### Statistical methods for primary and secondary outcomes {20a}

#### Analysis population

The analysis population includes an intention-to-treat (ITT) analysis population and a per-protocol (PP) analysis population. The ITT analysis includes the subjects who express intention to receive treatment, sign informed consent, and are randomized. The PP analysis includes the subjects who complete the trial according to the study protocol.

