#### Adverse event reporting and harms {22}

Adverse events include any symptom, syndrome, or disease that is present in a subject during the clinical study and would affect the subject’s health, as well as clinically relevant conditions found during laboratory or other diagnostic procedures. Researchers must record the time, duration, measures taken, and severity of AE in the common reporting format (CRF) table within 24 h of AE occurrence and report to the Ethics Committee. The researchers will evaluate the correlation with the drug under study and decide whether to discontinue the observation based on the condition, and the cases of drug discontinuation due to adverse reactions will be unblinding and followed. According to the clinical use of *Uncaria rhynchophylla*, *Semen Raphani*, and other traditional Chinese medicine decoction pieces and Val/Aml, we do not expect serious adverse events due to our intervention.

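### The adverse-event stopping wording conflicts between sections, and the adverse-event section does not separate stopping the drug from stopping observation

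*Protocol article*

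**What the plan says.** Five sections of the protocol article bear on what happens after an adverse event.

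- **Suspension criteria.** The only adverse-event item is "Adverse events (AEs), complications, or physiological changes that are fatal". The list also has a separate blood-pressure ground, which "will result in exclusion at any time during the study period", and a ground for voluntary withdrawal.
- **Criteria for discontinuing or modifying allocated interventions {11b}.** Besides withdrawal of consent, the grounds are "subsequent occurrence of a suspension criteria criterion (e.g., use of prohibited drugs), lack of compliance, and medical problems for stopping the intervention". The suspension list is thus included and added to.
- **Adverse event reporting and harms {22}.** Researchers judge the relation to the study drug and "decide whether to discontinue the observation based on the condition". It continues that "the cases of drug discontinuation due to adverse reactions will be unblinding and followed".
- **Procedure for unblinding if needed {17b}.** "The subjects should discontinue the study after unblinding".
- **Plans for assessment and collection of outcomes {18a}.** Randomised subjects are followed for four weeks, by telephone on day 3 and in week 3 and on site at weeks 2 and 4. No condition about causality is attached.

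Two analysis rules depend on who stays under observation. The per-protocol rule is: "The PP analysis includes the subjects who complete the trial according to the study protocol". In the ITT analysis, section {20c} fills missing data by last observation carried forward.

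**The concern.** Two things look wrong.

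First, the adverse-event item in the Suspension criteria appears to be met only when the event is fatal, and then there is no patient left to suspend. The other two sections plainly expect living patients to stop because of adverse events.

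Second, section {22} frames the researcher's decision as one about observation rather than about the drug. A patient who should only stop treatment could therefore also stop being measured. Its specific promise of follow-up is tied to a causality judgement.

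Safety is a stated objective of this four-week add-on trial in seven centres. If sites differ on whether observation continues after a stop, the outcome of some events is lost. Week-4 blood pressure, which carries the primary outcome, is then imputed when it could have been measured.

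**Working it through.** The point concerns wording. No figure in the plan has to be reproduced and no formula applies, so the check follows one living patient with a non-fatal adverse event through the sections.

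1. **Suspension criteria.** If the fatality condition governs the whole adverse-event item, this patient does not meet it, and neither does any other living patient. The item then has no function as a stopping criterion. The blood-pressure and voluntary-withdrawal grounds are independent of it.

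2. **Section {11b}.** The patient can be stopped here, under "lack of compliance, and medical problems for stopping the intervention". That phrase has no fatality limit. Because {11b} includes the suspension list, the two sections are cumulative, but the adverse-event ground in the first is far narrower than the medical ground in the second.

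3. **Section {22}.** The researcher judges relatedness and decides case by case, again without a fatality limit. The expectation that patients who stop the drug will be followed confirms that non-fatal stops are foreseen. What the researcher may end, however, is the observation.

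4. **The drug is stopped and the event is judged an adverse reaction.** Section {22} has this patient unblinded and followed. Section {17b} has an unblinded subject leave the study. The text does not settle whether such a patient is still seen at day 28.

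5. **The drug is stopped and the event is judged unrelated.** Section {22} makes no specific follow-up promise. Section {18a} still applies, since it covers all randomised subjects for four weeks. But the option in {22} to end observation can be read as overriding {18a}, and nothing says which prevails.

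6. **Effect on the analysis.** If observation ends in step 4 or step 5, the outcome of the event may not be recorded. The patient does not complete the trial and leaves the per-protocol set. In the ITT set the week-4 msSBP and msDBP are carried forward from the last value available.

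**Can a size be given?** No. The only loss figure in the article is the 20% allowance in the Sample size section (120 × 1.20 = 144 per group, so 24 per group). It covers loss for all reasons and is not split by cause. No expected rate of stopping for adverse events is stated.

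**The case against.** The strongest reply is that the sections should be read together. Section {11b} includes the suspension list and adds to it, and {22} says who decides, so a patient with a non-fatal event can be stopped. This stands. A reader might infer from the Suspension criteria alone that patients can be stopped only for fatal events and so lack protection. The documents do not support that, because it would require a site to treat the list as complete, and {11b} rules this out. Nor does {11b} stop patients for any medical problem whatever: its wording is limited to problems that warrant stopping the intervention.

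A second reply is grammatical: the fatality condition might attach only to physiological changes, leaving adverse events and complications unrestricted. This is possible, though less natural. It would not remove the conflict. An adverse event of any severity would then be a suspension criterion, which does not fit the case-by-case decision in {22}. A translation slip is also possible; the documents do not show one, and it would still need correcting.

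A third reply concerns follow-up. A reader might infer that events judged unrelated have no promised follow-up at all. That goes too far. Section {18a} gives every randomised subject four weeks of follow-up, and {22} requires the time, duration, severity and measures taken to be recorded for adverse events whatever their cause. What remains is the conflict between these provisions and the option to end observation.

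Finally, an article may leave the definition of a medical problem, or detailed rules for following an event, to the full protocol. That is accepted, and no point is made of it. The point rests on statements that the article prints and that do not agree.

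**Conclusion.** The point holds as a wording conflict with a consequence for data collection. On its natural reading the adverse-event ground in the Suspension criteria cannot operate, while {11b} and {22} foresee stopping for non-fatal events. Section {22} mixes stopping the drug with stopping observation, in conflict with {18a}, and its promise to follow unblinded cases conflicts with the study exit in {17b}.

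The effect on results is an inference from sections {17b}, {20c} and {22} and the Analysis population section. Stopping for adverse events is not a named outcome in the Outcomes section, so a reader should not infer that a defined endpoint is shown to be distorted. The effect depends on how many patients stop for adverse events and on how sites read the text; the documents give neither. It is worth correcting because safety is an objective, the week-4 blood pressure of these patients could be measured instead of imputed, and the change is small.

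**What to change.** Reconcile the Suspension criteria and sections {11b}, {17b}, {18a} and {22}:

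- Use one consistent wording for the adverse-event ground wherever it appears. The clinical threshold, and what is meant by the fatality condition, are for the sponsor and investigators to settle.
- Separate stopping the drug from stopping observation. State that stopping the drug for an adverse event does not end data collection: the outcome of the event and blood pressure are still collected at the existing contacts through day 28, in both arms and whatever the causality judgement, unless consent is withdrawn.
- Make {17b} and {22} agree on whether an unblinded patient remains under follow-up.
- Record the reason for stopping on the CRF.

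The cost is a wording amendment, one CRF item and a few more follow-up contacts for patients who would otherwise have left. The contacts already scheduled can serve.

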#### Secondary outcomes

The following are the secondary outcomes:
BP control rate at week 4 (defined as msSBP/msDBP < 140/90 mmHg).To evaluate the improvement of symptoms, the TCM syndrome scoring scale [22] will be used for evaluation (Additional file 3). To determine the degree of symptom improvement, we will refer to the Guiding Principles for Clinical Research on New Chinese Medicines [23]. Efficacy index = [(points before treatment − points after treatment)/points before treatment] × 100%. Significant effect: efficacy index ≥ 70%. Effectiveness: efficacy index ≥ 30%. Invalid: efficacy index < 30%.Other results include blood lipids, blood glucose, urinary microalbumin, uric acid, homocysteine, and hypersensitive C-reactive protein. It should be noted that no biological samples will be collected in our study.In addition, patient compliance will be assessed by counting the number of unused tablets returned at the scheduled visit. Table 1 shows the timing for all outcome measures in the study.

**Table 1 Tab1:** Outcome measures

Domain	Measurement	Time (days)

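### Stopping study tablets is not separated from leaving the study, so week-4 pressures that could be measured may be replaced by carried-forward values in the ITT analysis

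*Protocol article*

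**What the plan says.** All references are to the protocol article.

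- **Suspension criteria.** The list includes "Poor compliance of patients", use of prohibited drugs, voluntary withdrawal, and two adjacent items that the text runs together: "Incomplete data.Withdrawal due to various reasons, such as failure to participate in the follow-up". Reaching a sitting pressure of 200 systolic and/or 120 diastolic "will result in exclusion at any time during the study period".
- **Criteria for discontinuing or modifying allocated interventions {11b}.** The suspension criteria reappear here as reasons for stopping treatment, along with "lack of compliance, and medical problems for stopping the intervention".
- **Procedure for unblinding {17b}.** "The subjects should discontinue the study after unblinding".
- **Adverse event reporting and harms {22}.** The investigator may end observation depending on the patient's condition, yet "the cases of drug discontinuation due to adverse reactions will be unblinding and followed".
- **Analysis population {20a} and missing data {20c}.** "The ITT analysis includes the subjects who express intention to receive treatment, sign informed consent, and are randomized". Missing values in the ITT analysis are filled by LOCF. The PP set is those who complete according to protocol.
- **Outcomes {12}.** The primary outcome is the change in msSBP and msDBP from baseline to week 4. Among the secondary outcomes, "patient compliance will be assessed by counting the number of unused tablets returned at the scheduled visit".

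On-site visits are at weeks 2 and 4; day 3 and week 3 are telephone contacts.

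**The concern.** An ITT analysis is only as good as the outcome data behind it. Here one list of criteria serves both to stop the allocated treatment and to end participation. A site that follows the text could stop seeing a patient at the moment a criterion is met, although the patient could still attend at week 4.

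The reasons for leaving are not neutral. The pressure threshold is set on the primary outcome variable itself, so that exit is outcome-related by definition. Poor compliance and unblinding may be related to treatment or response; incomplete data need not be.

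What is at stake is the week-4 estimate. For these patients it would rest on a carried-forward value in place of a reading, and the resulting error depends on how many leave, when, and whether the arms differ. Incomplete data as a suspension ground also sits badly with a plan that imputes incomplete data.

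**Working it through.** **Step 1: the sections side by side.**

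| Event | One section | Another section |
|---|---|---|
| Suspension criterion met | Suspension criteria: exclusion wording at the pressure threshold | {11b}: a reason to stop the intervention |
| Unblinding | {17b}: patient leaves the study | {22}: patients unblinded after stopping the drug for adverse reactions are followed |
| Incomplete data | Suspension criteria: a suspension ground | {20c}: filled by LOCF in the ITT analysis |

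No section says that week-4 pressure is still measured once a criterion is met.

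**Step 2: what LOCF would then use.** With on-site visits only at weeks 2 and 4, an early exit usually leaves a week-2 or baseline value. Table 1 also lists pressure on days 3 and 21, but those contacts are by telephone.

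**Step 3: inputs (Sample size {14}).** DBP 8.3 (SD 5.53) for treatment and 6.3 (SD 4.31) for control. I read these as reductions, since they cannot be pressures after treatment. The difference is 8.3 − 6.3 = 2.0 mmHg. The common SD by the article's own averaging is √[(5.53² + 4.31²)/2] = 4.958. There are 144 per arm; tests are two-sided at 0.05.

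The plan's own 120 per arm does not reproduce. Its formula, 2 × multiplier × SD² / 2.0², gives 76.2 with the printed multiplier 6.2 and 129.0 with the printed z values, (1.96 + 1.28)² = 10.50. That is a separate matter and nothing below depends on it.

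**Step 4: reference power.** SE = 4.958 × √(2/144) = 0.584. 2.0/0.584 = 3.42; 3.42 − 1.96 = 1.46; power is 92.8%. This assumes a week-4 value for everyone and no dilution from stopping tablets.

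**Step 5: equal exits.** Assume a fraction d of each arm leaves before week 2, baseline is carried forward (change = 0), and the SD is held fixed. The difference is 2.0 × (1 − d).

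| d | Difference, mmHg | Power at 144 per arm |
|---|---|---|
| 5% | 1.9 | 90% |
| 10% | 1.8 | 87% |
| 20% | 1.6 | 78% |

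**Step 6: unequal exits, same assumptions.**
- 10% treatment, 20% control: 8.3 × 0.9 − 6.3 × 0.8 = 2.43 mmHg.
- 20% treatment, 10% control: 8.3 × 0.8 − 6.3 × 0.9 = 0.97 mmHg.
- No true effect (6.3 in both arms), 10% and 20%: 6.3 × 0.9 − 6.3 × 0.8 = +0.63 mmHg; reversed, −0.63 mmHg.

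0.63/2.0 is about a third of the planned difference.

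**The case against.** **The ITT set is intact.** A reader might infer that suspended patients are dropped from the ITT analysis, so that the rules contradict it. The documents do not support this. {20a} includes every consented, randomised patient, {20c} imputes their missing values, and completion according to protocol defines only the PP set. Calculations that delete excluded patients and average the rest describe the PP analysis, not this one. This objection stands: outside the wording on exclusion and incomplete data, the problem is loss of measurements, not loss of patients from the set.

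**Pressure exits may be few, and LOCF may not hide them.** Entry is at 160–179/100–109 mmHg and both arms receive valsartan/amlodipine. If the reading that triggers exclusion is recorded, LOCF carries that high value forward. This stands too; the baseline-carried illustration does not describe these exits.

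**Compliance is still recorded.** Tablets are counted at each follow-up. A patient found poorly compliant at week 2 already has a count, and one found at week 4 has lost nothing. At most, weeks 2 to 4 are cut off for some patients.

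**Some losses cannot be avoided.** Patients who withdraw or stop attending have left, and the adverse-event item in the list covers fatal events. Rewording recovers nothing there.

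**The article is condensed.** Visits after stopping treatment might be described in the full protocol. That would answer a complaint about silence. It does not answer what the article states: exclusion at any time, leaving the study on unblinding, incomplete data as a suspension ground, and a different account in {22}.

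**Conclusion.** The point holds as a fault of wording with consequences for the primary analysis. The suspension, discontinuation, unblinding and adverse-event sections do not separate stopping tablets from leaving the study, and {17b} and {22} disagree. Followed as written, they lose week-4 pressures that could have been obtained and substitute a week-2 or baseline value. They undermine the ITT analysis; they do not flatly contradict it.

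The size cannot be fixed from the documents, which give no exit rates by reason or arm. Under the stated assumptions, equal exits of 5% to 20% reduce the 2.0 mmHg difference to between 1.9 and 1.6 and power from about 93% to between 90% and 78%. A 10-point imbalance with no true effect creates a false difference of about 0.6 mmHg in either direction. Exits after week 2 would matter less if most of the effect is present by then. The gap to 93% also overstates the gain from measuring everyone, because patients off tablets would dilute the effect somewhat.

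A reader might take the plan's 20% as the number lost through these rules. It is a general allowance for loss, applied as 120 × 1.2 = 144, and serves above only as one point in a range.

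**What to change.** 1. Reconcile the Suspension criteria, {11b}, {17b} and {22} with {20a} and {20c}, saying for each event whether it stops study tablets, ends follow-up, or both. Leave the clinical stopping criteria and thresholds unchanged.
2. State that suspended or unblinded patients keep the scheduled week-2 and week-4 visits unless they withdraw consent, and are analysed as randomised.
3. Remove incomplete data as a suspension ground. Use it and missed follow-up only to define the PP set.

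The cost is mainly an amendment to the wording and a notice to the seven centres, since the visits are already scheduled. Some week-4 readings will be taken off study tablets, which an ITT analysis accepts. The article reports 57 patients already recruited; values from any who have left cannot be recovered.
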